#### 2.2.6. Provision for Post-Trial Care

As this is a diagnostic trial in which we are not testing any drug, such visits are not necessary. However, as this is an ancillary study embedded in the PyraPreg trial, post-trial cares have been scheduled until Day 63. These visits have been scheduled physically at the study site. Those who are not recovering well will be managed by the study clinician and recorded in PyraPreg case report forms (CRFs).

#### 2.2.7. Outcomes

The outcome (for the diagnostic screening and treatment follow-up parts) will be reported according to STARD principles [30]. We will report sensitivity, specificity, negative, and positive predictive values (primary outcome) of the mini-dbPCR-NALFIA test. The outcomes of the evaluations will be further analysed using 2 × 2 tables (at 95% confidence intervals), and comparisons of the performance of the diagnostic test under investigation will be made with standard diagnostic procedures in place and qPCR as the accepted reference test to determine the agreement between different tests (expressed as kappa values) [29]. 

To determine the utility of the mini-dbPCR-NALFIA test in monitoring treatment efficacy, parasite clearance will be assessed by mini-dbPCR-NALFIA and compared with qPCR. 

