## Abstract

The malaria parasite *Plasmodium falciparum* (*Pf*) can sequester in the placenta resulting in low density of peripheral parasitemia and consequently in false negative malaria diagnosis (by microscopy) in pregnant women. Moreover, the use of rapid diagnostic tests (RDTs) in diagnostic strategies, including those for the detection of a malaria infection during pregnancy, is constrained by either persistent malaria antigen (histidine-rich protein 2; HRP2) after successful treatment, leading to false positive test results, or by false negative results as previously mentioned due to parasite sequestration (which is further exacerbated due to the low limited of detection [LoD] of conventional RDTs) or to HRP2 deletion. Recently, a direct blood polymerase chain reaction combined with a nucleic acid lateral flow immunoassay (dbPCR-NALFIA) has been developed, which circumvents these challenges and has demonstrated its diagnostic potential in phase 1 and 2 studies. The PREG-DIAGMAL trial presented in this manuscript will assess the diagnostic performance of dbPCR-NALFIA for the diagnostic of malaria in pregnant women and its potential to monitor treatment efficacy in these subjects. The work is ancillary embedded in an ongoing EDCTP funded trial, the PyraPreg project (PACTR202011812241529) in which the safety and efficacy of a newly registered Artemisinin-Based Combination (Pyronaridine-Artesunate) is being evaluated in pregnant women. This is a Phase 3 diagnostic evaluation conducted in 2 African countries: Democratic Republic of the Congo (DRC) and Burkina Faso. Pregnant women fulfilling the inclusion criteria of the PyraPreg study will be also invited to participate in the PREG-DIAGMAL study. Diagnostic accuracy will be assessed following the WHO/TDR guidelines for the evaluation of diagnostics and reported according to STARD principles. Due to the lack of a 100% specific and sensitive standard diagnostic test for malaria, the sensitivity and specificity of the new test will be compared to the available diagnostic practice in place at the selected settings (microscopy and/or RDT) and to quantitative PCR as the reference test. This phase 3 diagnostic study is designed towards the evaluation of the performance of a new diagnostic tool for the screening of malaria and the monitoring of treatment in pregnant women under real conditions life. If successful, the dbPCR-NALFIA could be a valuable tool to add to the diagnostic arsenal for malaria, in particular during pregnancy. Trial registration: Pan African Clinical Trial Registry database (PACTR202203780981413). Registered on 17 March 2022.

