These above-mentioned evaluations do not include pregnant women who are however very vulnerable to malaria infections [24,25]. Indeed, *P. falciparum* can sequester in the placenta during pregnancy, resulting in low peripheral parasitemia. Consequently, malaria diagnostic tests are often false negative in pregnant women who actually do have a *P. falciparum* malaria infection [26,27] and they do not receive adequate treatment. Due to its very high analytical sensitivity, the mini-dbPCR-NALFIA test could be a good diagnostic test to properly detect malaria in pregnancy (MiP). 

In addition, the treatment of malaria in pregnancy needs to be safe and efficient. Currently most cases of MiP are treated with ACT [24,28]. It is however difficult to measure the effect of treatment in these specific cases. The mini-dbPCR-NALFIA might provide a suitable platform to follow treatment efficacy as well.

The main aim of the study is to evaluate the diagnostic performance of the mini-dbPCR-NALFIA test for MiP. In order to achieve that, the following study objectives will be achieved through a dedicated diagnostic trial focussing on malaria infection in pregnant women.

The planned work has the following primary objective: to assess the diagnostic accuracy of the mini-dbPCR-NALFIA test for the diagnosis of malaria in pregnancy compared to routine diagnostic procedure(s) in place (microscopy and/or RDTs) and qPCR (as reference test). The secondary objectives of the trial are:

To determine the utility of the mini-dbPCR-NALFIA to monitor anti-malaria treatment with ACT efficacy in pregnancy during a follow-up period of 63 days.

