## 2. Design/Methods

The trial design is presented below by following the SPIRIT guidelines. This trial is an ancillary study embedded in an EDCTP funded drug trial (Safety and Efficacy of a newly registered Artemisinin-Based Combination (Pyronaridine-Artesunate-PYRAMAX^®^) (PyraPreg [PACTR202011812241529]). The planned phase 3 diagnostic study consists of two components.

The first component will assess the diagnostic accuracy of the mini-dbPCR-NALFIA test for the diagnosis of malaria in pregnant women (**diagnostic screening part**). The study hypothesis for this component is: “mini-dbPCR-NALFIA will offer an improved diagnostic platform over microscopy and/or currently available RDTs for the detection of malaria infection in pregnant women”. This will be studied through a phase 3 diagnostic trial. Diagnostic performance will be assessed following the WHO/TDR guidelines for the evaluation of diagnostics [29] and the results will be reported according to STARD principles [30]. This phase 3 evaluation will screen pregnant women at the point of enrolment for the main PyraPreg trial for the presence of malaria in both Burkina Faso and DRC. Potential study participants (≥15 years of age, pregnant, able to provide informed consent) will be identified during their visits to the study health facility and asked to participate in the diagnostic study. Consequently, both malaria negative, as well as malaria positive (confirmed by the standard diagnostic practices in place), will be tested for this screening part of the study. An additional blood sample (finger prick blood), next to the clinical sampling performed in the framework of the PyraPreg project at the point of screening, will be collected from the same women. This sample will be analysed by mini-dbPCR-NALFIA (index test) and qPCR (as reference test). The results of the experimental diagnostic testing will not be used to make any decisions about the clinical management of pregnant women.

For the **treatment follow-up part** (second component), we will recruit the same women who have been recruited for the main PyraPreg trial (in Burkina Faso only) and who will be followed up for a period of 63 days. At each of their planned study visit (at days 1, 2, 3, 7, 14, 21, 28, 35, 42, 49-56, and 63) we will obtain an additional blood sample for qPCR and mini-dbPCR-NALFIA testing.

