### 2.2. Interventions

#### 2.2.1. Explanation of the Choice of Comparator

The diagnostic performance of the mini-dbPCR-NALFIA for the screening of malaria and the follow-up of malaria treatment in pregnant women will be compared to the standard malaria diagnostic practices in place in the 2 participating countries (i.e., microscopy and/or rapid diagnostic test). Established qPCR will be used as the reference standard.

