### 2.6. Statistical Methods

#### 2.6.1. Statistical Methods for Primary and Secondary Outcomes

As mentioned above, the outcomes of the evaluations will be analysed using 2 × 2 tables (at 95% confidence intervals), and comparisons will be made with standard diagnostic procedures in place and qPCR as the accepted reference test. Positive and Negative Predictive Values will be calculated. The sensitivity and specificity of the mini-dbPCR-NALFIA are assumed to be at least 90% [23]. The utility of the mini-dbPCR-NALFIA to monitor treatment success (in terms of recurrent parasitemia) will be compared to qPCR. The association between the molecular test results obtained during the follow-up will be assessed using logistic regression models.

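### The screening hypothesis is that mini-dbPCR-NALFIA improves on microscopy and/or RDT, but the only between-test measure the article names is kappa agreement, which has no direction and cannot show improvement.

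*Protocol article*

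**What the plan says.** - **Hypothesis (protocol article, section 2, Design/Methods).** For the screening component: "mini-dbPCR-NALFIA will offer an improved diagnostic platform over microscopy and/or currently available RDTs for the detection of malaria infection in pregnant women". This is a directional claim about the index test relative to routine tests.
- **Primary objective (section 1, Background).** Accuracy of the index test "compared to routine diagnostic procedure(s) in place (microscopy and/or RDTs) and qPCR (as reference test").
- **Primary outcome (section 2.2.7).** "We will report sensitivity, specificity, negative, and positive predictive values (primary outcome) of the mini-dbPCR-NALFIA test". The same paragraph adds 2 × 2 tables with 95% confidence intervals and comparisons with routine procedures and "qPCR as the accepted reference test to determine the agreement between different tests (expressed as kappa values").
- **Statistical methods (section 2.6.1).** The 2 × 2 tables are repeated, and "comparisons will be made with standard diagnostic procedures in place and qPCR as the accepted reference test". The one model named is a logistic regression for the follow-up results.
- **Reference standard (section 2.2.1).** "Established qPCR will be used as the reference standard". Microscopy and/or RDT are the comparator.
- **Abstract.** "the sensitivity and specificity of the new test will be compared to the available diagnostic practice in place at the selected settings", and also to qPCR as the reference test.
- **Sample size (section 2.2.9).** 555 women, from a confidence interval for a single proportion and a prevalence of about 25%.

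**The concern.** The question is whether the new test is better than current practice. The measure named for comparing the tests asks how often they agree, and low agreement can mean that either test is the worse one.

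The Background expects the two to differ. It describes low-density infections in pregnancy that microscopy and RDT miss, antigen that persists after treatment and makes RDTs falsely positive, and an index test 10 to 100 times more analytically sensitive than conventional diagnostics. Each infection that only the index test correctly finds, and each false-positive RDT that it correctly rejects, lowers agreement. A good index test could therefore show modest kappa values, and nothing in kappa would tell the reader that the disagreement is in its favour.

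The Discussion says that success would supply the evidence for introducing the test into routine care. That needs a directional comparison with what is used now.

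**Working it through.** **1. The plan's own figure.** Section 2.2.9 gives p ± 1.96√[p(1 − p)/n]. The half-width is not stated; I assume 5 points. With p = 0.90 (section 2.6.1):

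- infected women: 1.96² × 0.90 × 0.10 / 0.05² = 138.3, so 139
- total: 138.3/0.25 = 553, or 139/0.25 = 556

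This brackets the stated 555. Half-widths of 4 and 6 points give 864–868 and 384–388 and do not match. So 555 fits a one-test precision calculation with no comparative element.

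**2. Kappa has no direction.** κ = (po − pe)/(1 − pe). Take prevalence 0.25, both specificities 1, and the positives of the less sensitive test contained in those of the other.

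- Index 0.90, routine 0.60: both positive 0.150, one positive 0.075, both negative 0.775. po = 0.925, pe = 0.6925, κ = 0.2325/0.3075 = 0.756.
- Index 0.60, routine 0.90: the discordant cell changes side, and κ is again 0.756.

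**3. A test that detects every infection.** Prevalence is from the protocol. The rest are assumptions, since the article gives no routine-test accuracy: routine sensitivity 0.60 and specificity 0.99, index sensitivity 1.00 and specificity 0.98, false positives independent. Per 1,000 women:

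| | Routine + | Routine − |
|---|---|---|
| Index + | 150.15 | 114.85 |
| Index − | 7.35 | 727.65 |

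Of the 114.85 index-only positives, 250 × 0.40 = 100 are true infections that routine testing missed.

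- po = 0.8778; pe = 0.265 × 0.1575 + 0.735 × 0.8425 = 0.6610; κ = 0.2168/0.3390 = 0.64
- apparent specificity against routine = 727.65/842.50 = 86%
- apparent PPV against routine = 150.15/265.00 = 57%

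For routine sensitivity 0.50 to 0.80, this κ runs from 0.55 to 0.80 and apparent specificity from 84% to 92%.

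**4. How kappa moves as the index test improves** (same assumptions, routine sensitivity 0.60):

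| Index sensitivity | 0.60 | 0.90 | 1.00 |
|---|---|---|---|
| κ with routine, routine-detected infections nested in index-detected | 0.92 | 0.70 | 0.64 |
| κ with routine, independent errors | 0.47 | 0.60 | 0.64 |
| κ with qPCR | 0.65 | 0.89 | 0.96 |
| Apparent specificity vs routine, nested | 98% | 89% | 86% |
| Apparent specificity vs routine, independent | 91% | 88% | 86% |

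The direction of κ with the routine test depends on how errors overlap. Only apparent specificity against the routine test falls under both structures.

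**5. What 555 gives for a paired comparison.** About 139 qPCR-positive women, index sensitivity si = 0.90, routine sensitivity sm assumed, two-sided 5%. With p10 = si(1 − sm), p01 = (1 − si)sm, pd = p10 + p01 and d = p10 − p01, power = Φ[(d√n − 1.96√pd)/√(pd − d²)].

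For sm = 0.75: p10 = 0.225, p01 = 0.075, pd = 0.30, d = 0.15, so power = Φ[(1.768 − 1.074)/0.527] = Φ(1.32) = 0.91.

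| Routine sensitivity | 0.60 | 0.70 | 0.75 | 0.80 | 0.85 |
|---|---|---|---|---|---|
| Power, independent errors | >0.99 | 0.99 | 0.91 | 0.64 | 0.24 |
| Power, near-nested (p01 = 0.02) | >0.99 | >0.99 | 0.99 | 0.89 | 0.50 |

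**The case against.** **Kappa is not the whole plan.** Index sensitivity, specificity and predictive values are the primary outcome, qPCR is the reference throughout, and the abstract announces an accuracy comparison with routine practice. This stands. A reader with each test's results against qPCR could compare them informally. It does not remove the conflict, because section 2.2.7 gives agreement as the purpose of the comparison and kappa as its measure.

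**A condensed article need not name a test.** The full protocol or analysis plan may specify McNemar's test. This also stands: a reader might infer that the hypothesis will never be tested, and the article cannot show that. The point rests on the measure it does state.

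**A reader might infer that kappa gets worse as the new test gets better.** That is not general. Against the routine test it falls under nesting but rises with independent errors, and against qPCR, which the same sentence covers, it rises.

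**A reader might infer that microscopy or RDT will serve as the reference standard**, so that true infections are labelled false positives. The wording in 2.2.7 and 2.6.1 is loose enough to allow this, but no section says so and 2.2.1 points the other way. The 86% apparent specificity shows what that reading would produce, not what the plan commits to.

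**Conclusion.** The point holds in a limited form. The article pairs a superiority hypothesis with a symmetric agreement measure as its only named between-test statistic. That measure cannot show which test is better, and this needs no assumption about accuracy.

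The size of the effect does rest on assumptions. An index test that detects every infection would show a kappa of about 0.64 with a routine test of 60% sensitivity, and 0.55 to 0.80 across routine sensitivities of 50% to 80%, given prevalence 25%, routine specificity 99% and index specificity 98%.

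The primary outcome, the reference standard and the one-test sample size do not depend on kappa and are not called into question.

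**What to change.** In sections 2.2.7 and 2.6.1, state that the section 2 hypothesis is assessed with qPCR as reference by:

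- the paired difference in sensitivity among qPCR-positive women, and
- the paired difference in specificity among qPCR-negative women,

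each for NALFIA minus microscopy and separately for NALFIA minus RDT, in the women who had that comparator, with 95% confidence intervals and McNemar's test. Keep kappa as descriptive, and say that microscopy and RDT are comparators, not reference standards.

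This changes wording and analysis only. Routine test, index test and qPCR are already planned in the same women, so no further sampling is needed.

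The cost is in power. The comparison is well supported only if routine sensitivity is about 75% or lower; with independent errors it drops to 64% at 80% and 24% at 85%. Because the article says microscopy and/or RDT, one comparator may not be done in every woman, and its power would then be lower still. State the routine sensitivity assumed, and the resulting power or interval width, before the data are analysed.

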#### 2.2.8. Participant Timeline

Participants will be asked to provide a clinical specimen at the study visit defined by the PryraPreg trial (on the day of screening and days 1, 2, 3, 7, 14, 21, 28, 35, 42, 49–56, and 63 for those who have entered the treatment evaluation).

#### 2.2.9. Sample Size

The sample size for the diagnostic screening component has been calculated according to the expected disease prevalence in the Nanoro health centre catchment area to give adequate statistical power to test sensitivity and specificity [29]. Sample size calculation is based on a 95% confidence interval and using the following equation [29,30]: p +/− 1.96 × √[p(1 − p)/n] where p= sensitivity (or specificity) measured as a proportion and n = number of samples from infected people (or for specificity from non-infected).

The sample size calculation is further based on the estimated prevalence of malaria in pregnancy in the study area, which is around 25% [32]. Based on these assumptions, the following sample size has been determined: 555 cases need to be recruited for the screening component.

For the treatment follow-up component, we will be following the number of cases that are being planned to be recruited for the main PyraPreg trial. In this case, it is expected that we can follow-up with around 138 pregnant women who are under anti-malaria treatment for a period of 63 days.

#### 2.2.10. Recruitment

Prior to the start of the study, communities and community leaders will be informed about the purpose of the study to enhance participation. All study sites have a sufficiently large population and malaria incidence to reach the projected sample size.

### 2.3. Assignment of Intervention: Allocation

#### 2.3.1. Sequence Generation

Not applicable, as there will be no allocation to different study arms. All subjects will be subjected to the same procedures; i.e., collection of a blood sample for diagnostic testing.

#### 2.3.2. Concealment Mechanism

Not applicable, as there will be no allocation to different study arms. All cases will receive the same intervention.

#### 2.3.3. Implementation

Not applicable, as there will be no allocation to different study arms. All cases will receive the same intervention.

### 2.4. Assignment of Interventions: Blinding

There is no procedure for blinding as all participants will be following the same study procedure. 

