To circumvent these challenges, a simple molecular diagnostic platform to diagnose malaria has been developed that can be used near patient (PoC). This platform combines direct-on-blood (db)PCR with a nucleic acid lateral flow immunoassay (NALFIA) to detect *Plasmodium* species in a multiplex format [21]. The NALFIA is a simple read-out system, comparable to a dipstick, to visualize amplicons. The dbPCR-NALFIA system has an analytic sensitivity of 1.0 to 0.1 parasite/µL of blood (10–100 times more sensitive than conventional malaria diagnostics) with a high sensitivity and specificity in clinical settings [21]. Importantly, the platform allows for direct amplification of *Plasmodium* DNA in whole blood [22] by utilizing specific enzymes and buffers that are able to withstand the inhibitory effects usually encountered when directly amplifying DNA in blood. This avoids contamination-prone and labour-intensive parasite DNA extraction from a clinical sample. This dbPCR-NALFIA has passed laboratory evaluations and trials in disease endemic countries [22,23]. Recently the dbPCR-NALFIA has been optimised by using a mini-PCR system (battery operated, reducing its dependency on electricity, solar powered and controlled via an application on a mobile telephone) thereby enhancing its field applicability. Currently, the platform (mini-dbPCR-NALFIA) is undergoing phase III diagnostic evaluations in the framework of the European & Developing Countries Clinical Trials Partnership (EDCTP) funded DIAGMAL project (PACTR202202766889963 and ISRCTN13334317) in 5 African countries: Ethiopia, Burkina Faso, Namibia, Sudan, and Kenya. In this project, the diagnostic performance of the mini-dbPCR-NALFIA test will be evaluated in the context of different malaria epidemiology settings. Furthermore, a cost effectiveness evaluation of the implementation of this new diagnostic platform will be performed in the framework of this study.

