#### 2.1.2. Eligibility Criteria

The screening study will include cases who fulfil the following inclusion criteria:Gestation ≥16 weeks and <37 weeks as assessed by ultrasound (if possible) or uterine height or late menstrual period;Age: ≥15 years;Residence within the health facility catchment area;Ability to provide written informed consent.

The treatment follow-up study will include cases that have met the inclusion criteria for the PyraPreg study. These have been defined as follows:Gestation ≥16 weeks and <37 weeks as assessed by ultrasound (if possible,) or uterine height or late menstrual period;*P. falciparum* mono-infection (by microscopy) of any density, regardless of symptoms and HIV status;Haemoglobin ≥7 g/dL;Age: ≥15 years;Residence within the health facility catchment area;Willing to adhere to study requirements and to deliver at the health facility;Ability to provide written informed consent.

Not meeting the inclusion criteria will result in exclusion from the study.

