#### 2.2.2. Intervention

Both RDT and/or microscopy will be performed as part of the routine diagnostic procedures in place at the study sites. RDT will be performed according to the manufacturer procedures. Thin and thick blood films will be prepared and Giemsa stained. Blood slides will be independently read by 2 expert microscopists. Parasite density will be calculated by counting the number of asexual parasites per 500 leukocytes in the thick blood film, based on an assumed WBC of 8000/µL by light microscopy at 1000× magnification. In addition to routine diagnostic procedures in place, an additional blood sample (preferably finger prick blood) will be collected for test evaluation (index and reference tests). Blood samples will be properly labelled with patients’ initials, inclusion number, protocol number, scheduled study visit, and the date of the sampling. For the index test (mini-dbPCR-NALFIA) <20 μL of blood (collected in an EDTA tube) is needed. For reference testing (qPCR), three blood spots will be collected on Whatman 3 filter paper [31]; one sample for qPCR, the second and third sample for QC procedures (10%) or back-up.

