#### 2.5.4. Confidentiality

Every possible measure to ensure that all personal data collected during the study will be appropriately protected will be taken. The collection of personal information will be restricted to meet the objectives of the study, and only data relevant to the execution of the study and interpretation of data will be collected. Collected information will be kept for a minimal time period, which is regulated by national or international law. All personal data collected during the study will be kept confidential. After the collection of blood samples, a numerical identifier will be assigned to each sample. None of the results will be published with individual name identification. At the end of the project, all names will be destroyed. All personalised data forms, signed informed consent forms and other personalised information will be kept under lock and will be available only to the project coordinator, principal investigators, and data managers. Information stored in the electronic database will be protected by unique usernames and passwords, which will be made only available to appropriate authorised personnel. Data entry will be checked independently on site by the research clinician and/or by the PI to ensure accuracy. The collected information will never be transferred to countries lacking appropriate data protection or made available without restriction to third parties that are not directly linked to the project.

Plans for collection, laboratory evaluation, and storage of biological specimens for genetic or molecular analysis in this trial/future use

Blood samples will be collected for molecular analysis by PCR, which is used as a reference test for the diagnostic procedures followed in this trial. This work will be restricted to the assessment of the presence of *Plasmodium* species only. There will be no analysis of human genetic material. Collected specimens could be used for future diagnostic test development and evaluation and explicit informed consent from study participants will be obtained for this.

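### Section 2.4 declines blinding for a treatment-allocation reason, so the plan permits the index and reference tests to be read unmasked; this can bias accuracy in either direction

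*Protocol article*

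**What the plan says.** Section 2.4 of the protocol article consists of one sentence: "There is no procedure for blinding as all participants will be following the same study procedure". It follows three allocation items, all marked not applicable because there are no arms. The one on concealment reads "Not applicable, as there will be no allocation to different study arms. All cases will receive the same intervention".

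Other sections bear on who could know what when a test is read:

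- **Index read-out (1. Background):** "The NALFIA is a simple read-out system, comparable to a dipstick, to visualize amplicons". The result is judged by eye.
- **Source of the samples (2. Design/Methods):** index test and qPCR both use the additional finger-prick sample.
- **Labels (2.2.2):** samples carry the patient's initials and "inclusion number, protocol number, scheduled study visit, and the date of the sampling".
- **Identifier (2.5.4, Confidentiality):** "After the collection of blood samples, a numerical identifier will be assigned to each sample".
- **Independence (2.2.2):** "Blood slides will be independently read by 2 expert microscopists". This is the only independence between readers that the article states.
- **Entry to follow-up (2.1.2):** women must have a *P. falciparum* "mono-infection (by microscopy) of any density, regardless of symptoms and HIV status", so all of them are known to be microscopy-positive at entry.
- **Staff (2.5.1):** trained study staff perform the tests and record the data; no separation of readers is described.
- **Outcomes (2.2.7):** sensitivity, specificity and predictive values are primary, kappa measures agreement between tests, and parasite clearance by the index test is compared with qPCR.

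**The concern.** That every participant undergoes the same procedures is a good reason not to mask participants to an allocation. It has no bearing on whether the person looking at a NALFIA strip knows the qPCR, microscopy or RDT result, or whether the qPCR operator knows the strip result. In an accuracy study those are the judgements that need protecting, because each 2 × 2 table assumes that its two results were obtained independently of each other.

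A faint line on a strip is where outside knowledge can decide the call. Under the plan as written, the label links the sample to the woman and so to her other results. In follow-up it also gives the visit, and a reader may expect a positive soon after enrolment and a negative at day 63.

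At stake are the primary outcome, the kappa values and the clearance comparison. A confidence interval does not reveal this kind of error, because it reflects sampling variation only.

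**Working it through.** **1. The plan's sample size.** Section 2.2.9 gives the interval p ± 1.96 × √[p(1 − p)/n], a prevalence of about 25% and a total of 555. Section 2.6.1 assumes sensitivity and specificity of at least 90%. No half-width is stated; I assume 5 points.

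- Infected women: 1.96² × 0.90 × 0.10 / 0.05² = 138.3, rounded up to 139.
- Total: 138.3 / 0.25 = 553.2 (554 rounded up), or 139 / 0.25 = 556.

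The stated 555 lies between these. With p of 0.90 or 0.95 and half-widths of 3, 4, 5 or 6 points, no other combination comes near it. So 5 points is a fair back-calculation, but it is not a figure in the article.

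With 555 screened, 555 × 0.25 ≈ 139 are infected, and the half-width for sensitivity is 1.96 × √(0.09/139) ≈ 5.0 points.

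**2. How far a few altered readings move the result.** Each changed reading among 139 infected women shifts sensitivity by 100/139 = 0.72 points, up or down. If a share s of the misses is turned positive, observed sensitivity = true + s × (1 − true). At the article's 90% there are 139 × 0.10 = 13.9 misses. The kappa column also lets the same share of false positives be changed (90% specificity, 25% prevalence). At s = 0, observed agreement is 0.90, chance agreement is 0.30 × 0.25 + 0.70 × 0.75 = 0.60, and kappa = 0.30/0.40 = 0.75.

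| Share s (assumed) | Misses changed | Observed sensitivity | Shift (points) | Kappa |
|---|---|---|---|---|
| 0 | 0 | 90.0% | 0 | 0.75 |
| 10% | 1.4 | 91.0% | 1.0 | 0.77 |
| 20% | 2.8 | 92.0% | 2.0 | 0.80 |
| 33% | 4.6 | 93.3% | 3.3 | 0.83 |

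The shares are assumptions; nothing in the article supplies them.

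**3. Direction.** The table shows one direction only: index readings moved toward a known qPCR result. The Background section puts expert microscopy's detection limit at around 10 parasites/µL and the index test's at 0.1 to 1.0. Infections between those densities are where the index test should gain. For them microscopy would usually be negative, so a reader who knew that might call a faint true line negative. Sensitivity against qPCR would then fall by 0.72 points per reading, and the improvement hypothesised in section 2 would be partly hidden.

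**4. Which knowledge matters where.** In screening each woman gives a single sample at one visit, so the visit label tells the reader nothing. The routes there are the qPCR, microscopy and RDT results. Visit day and earlier results matter only in follow-up.

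**The case against.** The strongest reply is that section 2.4 answers a SPIRIT item headed as assignment of interventions, so it may speak only of allocation and leave reader masking to procedures not shown; section 2.7.4 does refer to study-specific SOPs. A numerical identifier is assigned to each sample, slides are read independently by two microscopists, and qPCR from filter paper may be run later and elsewhere.

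Part of this stands. The article does not say that readers will see other results, and it gives neither the order nor the place of reading. A reader might infer that unmasked reading is planned; the text only permits it. Later qPCR would limit its influence on the strip reading, though not the influence of a known strip result on qPCR calls, or of routine results on the strip.

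The rest does not remove the point. The sentence says that no procedure exists and gives a reason, which is more than leaving a detail out. The identifier is described as a confidentiality measure, and nothing says that readers see only that code; section 2.2.2 puts initials and visit on the label. The microscopists' independence is from each other.

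A reader might also infer that accuracy will be biased upward. The documents do not support that, for the reason in step 3 of the working. Nor do they support calling the damage wholly irreversible: section 2.2.2 keeps further blood spots for quality control or back-up, so some qPCR could be repeated masked.

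**Conclusion.** The point holds as a defect in what section 2.4 states. Its reason does not fit the design, and the plan as written allows the index and reference tests to be read with knowledge of each other, of routine results and, in follow-up, of visit day and earlier results. This can bias sensitivity, specificity, kappa and the clearance comparison.

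Neither direction nor size can be derived from the documents. The shift of 1.0 to 3.3 points rests on 90% true sensitivity, about 139 infected women and an assumed 10% to 33% of misses being changed. It is smaller than the back-calculated half-width of about 5 points but, unlike sampling error, would not show in the interval. It illustrates scale and is not an estimate. The point is worth correcting because it touches the primary outcome and the remedy is cheap.

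**What to change.** Replace the sentence in section 2.4 with wording to this effect:

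- The NALFIA reader and the qPCR operator are each unaware of the other's result, of microscopy and RDT results and, in follow-up, of visit day and earlier results.
- Index and reference samples reach them under only the numerical identifier of section 2.5.4, without initials or visit. Amend the labelling text in section 2.2.2 to match.
- Each records the result before seeing any other.
- Microscopy and RDT readers are unaware of index and qPCR results. Routine results are released as usual, so that standard practice (section 2.2.3) and PyraPreg enrolment are not delayed.

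The masking should stop there. Holding every result until all the others are locked, or masking routine readers to clinical data, could hold back microscopy and RDT results that the main trial needs.

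Enrolment began in November and December 2021 (Trial status), so results already read unmasked should be flagged and a sensitivity analysis run without them. That analysis loses precision: if half the readings were excluded, about 69 infected women would remain and the half-width would be 1.96 × √(0.09/69.4) ≈ 7.1 points.

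The cost is small: coded labels, a code key and SOP wording. Sample size, visits and clinical care do not change.
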